### Treatment planning

A Rectal Displacement Device (RDD) is to be used with the main options being the transperineal application of SpaceOAR, or transanal insertion of a Rectafix™ to increase distance from rectum to prostate [16, 17].

### Simulation

Intraprostatic fiducial markers will be inserted at least 7 days prior to treatment planning. An appropriate RDD is selected for rectal separation. A temporary In-Dwelling urinary Catheter (IDC) can be inserted for planning scans to aid urethral contouring at clinician’s discretion. Patients will be instructed to follow bladder and bowel preparation to achieve an empty rectum and full bladder.

A planning Computed Tomography (CT) scan is acquired in both SBRT and EBRT treatment positions. Minimum CT slice thickness of 2.5 mm, scanning from L4 to include whole pelvis to below the perineum. A SBRT planning MRI with RDD in-situ is to be performed within 1 h of CT to minimize effect of prostate deformation caused by variable bowel filling.

### SBRT treatment planning

CT-MRI fusion of planning scans using prostatic fiducial registration is performed.

The CTVsbrt is the prostate plus any observed extraprostatic disease, either due to T3a extracapsular extension (ECE) or seminal vesicle invasion (SVI). For SVI include disease observed on MRI only for the boost. The SBRT Planning Target Volume (PTVsbrt) expansion is 5 mm in all directions from CTVsbrt, except posteriorly where it is 3 mm.

Table 1 lists the critical structure contouring guidelines.

**Table 1 Tab1:** Critical structure contouring guidelines

Structure name	Description
Rectal Wall	Contour as a 3 mm thick wall structure from recto-sigmoid junction to lower aspect of ischial tuberosities.
Rectal Mucosa	Solid structure corresponding to the internal cylindrical space central to the inner surface of the rectal wall.
Rectum Posterior Wall	This is the most posterior 15 mm of rectal wall
Bladder	Contour the whole organ as a solid structure.
Penile Bulb	Contour from MRI.
Prostatic urethra Planning Target at Risk Volume (PRV)	Contour urinary IDC within prostate, and add 1 mm radial expansion for the PRV. If no IDC used, estimate urethral position, and add 3 mm radial expansion.
Neck of Femur	Contour the Left and Right NOF as solid structures to the level of the ischial tuberosity.

Inverse planned IMRT or related modulated dose techniques (Tomotherapy, Cyberknife [CK] or Volumetric Modulated Arc Radiotherapy [VMAT]) are required. For static field IMRT, between 5 and 8 fields recommended. Photon energies of 6–10 MV, with higher energies not recommended due to the higher potential for neutron scatter with the large daily doses. An exception is patients with large separations where 1–2 higher energy beams may be helpful in improving dose distribution, but only if all other beams are 6–10 MV. Non-coplanar beams are allowed. VMAT may provide the advantage of more rapid treatment time reducing the need for interim imaging to manage intrafraction motion.

SBRT dose constraints should be met as per Table 2:

**Table 2 Tab2:** SBRT dose constraints. (TD = Target dose)

Constraint	Per-Protocol	Minor Variation	Major Variation
CTVsbrt D98^a^	> 100% TD	95–100% TD	< 95% TD
PTVsbrt D50^a^	< 105% TD	105–110% TD	> 110% TD
PTVsbrt D90^a^	> 100% TD	95–100% TD	< 95% TD
PTVsbrt D95^a^	> 95% TD	90–95% TD	< 90% TD
PTVsbrt D99^a^	> 16 Gy	15–16 Gy	< 15 Gy
PTVsbrt Dmax to 0.1cc	< 110% TD	110–120% TD	> 120% TD
PTVsbrt Dmax	Not within a critical structure		
Rectal Wall Dmax to 0.1cc	< 17 Gy	17–17.5 Gy	> 17.5 Gy
Rectal Wall V16 Gy	< 0.5cc	0.5-1cc	> 1cc
Rectal Wall V14 Gy	< 3cc	3-5 cc	> 5cc
Rectal Wall V12 Gy	< 30%	30–40%	> 40%
Rectal Wall V10 Gy	< 40%	40–50%	> 50%
Rectal Wall V8 Gy	< 60%	60–70%	> 70%
Rectal Mucosa Dmax to 0.1cc	< 15 Gy	15–15.5 Gy	> 15.5 Gy
Rectal Mucosa V14 Gy	< 0.5cc	0.5-1cc	> 1cc
Rectum Posterior Wall	< 8.5 Gy	8.5–9.5 Gy	> 9.5 Gy
Bladder Dmax to 0.1cc	< 110% TD	110–120% TD	> 120% TD
Bladder V19 Gy	< 10cc	10-15cc	> 15cc
Bladder V17 Gy	< 15%	15–20%	> 20%
Bladder V9 Gy	< 50%	50–60%	> 60%
Urethra PRV Dmax to 0.1cc	< 110% TD	110–115% TD	> 115% TD
Urethra PRV V105% TD	< 5%	5–15%	> 15%
Neck of Femurs Dmax to 0.1cc	< 8 Gy	8–9 Gy	9 Gy
Penile Bulb Dmax to 0.1cc (Recommended)	100% TD	100–105% TD	> 105% TD
Penile Bulb V10 Gy (Recommended)	<3cc	3-5cc	> 5cc
Intermediate Dose Spillage: ratio of volumes receiving 50% TD to 100% TD	< 4	4–5	> 5
Total Monitor Units	< 3× Dose in cGy	3–3.5× Dose in cGy	> 3.5× Dose in cGy
High Dose Conformation: Volume receiving 100% of TD divided by volume of PTVsbrt	< 1.1	1.1–1.2	> 1.2

^a^Where Urethra has been limited to 19 Gy, these volumes may exclude the urethra: eg. CTVsbrt D98 = CTVsbrt – Urethra PRV D98

Aim to encompass the entire PTVsbrt with 19Gy minimum. However, PTVsbrt coverage may be compromised posteriorly to a minimum of 16Gy only where necessary in order to meet rectal dose constraints. Aim for 16Gy isodose line to only encompass posterior PTVsbrt where there is overlap between PTVsbrt and Rectum (see Figs. 2 and 3).

**Fig. 2 Fig2:**
[figure not shown]
Transverse CT view of example dose distribution adhering to planning constraints with Rectafix™ displacing rectum posteriorly

**Fig. 3 Fig3:**
[figure not shown]
Sagittal CT view of example dose distribution. Note the high dose sparing of the Urethral PRV, and posterior PTVsbrt dose compromise to meet rectal dose constraints

The mechanism for the stepwise SBRT dose escalation is as follows:

A minimum of 20 men in total are to complete treatment without > 15% suffering a grade 3 acute toxicity or any episodes of grade 4 acute toxicity at a particular dose level. The individual centre must also accrue ≥5 patients at the previous dose level prior to exploring dose escalation. Once this accrual trigger has been met, increase the dose by 1 Gy to D98% of the volume CTVsbrt minus urethral PRV. The first dose escalation will therefore be to 20 Gy. This process can be followed a maximum of three times, to a maximum CTVsbrt-Urethral PRV D98 of 22 Gy.

A credentialing “dummy run” will need to be performed on a previous patient data set to demonstrate to an external reviewer the feasibility of achieving these new dose constraints. The first three patients planned at each dose level will be subject to a real-time QA process. An external RO review of target delineation, OAR doses and plan quality shall be undertaken before any planned treatment is delivered.

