**Methods:**

Eligible patients have intermediate or high risk PC. PROMETHEUS explores the safety, efficacy and feasibility of multiple Australian centres cooperating in the delivery of Prostate Stereotactic Body Radiotherapy (SBRT) technology. A SBRT boost component Target Dose (TD) of 19Gy in two fractions is to be delivered, followed by a subsequent EBRT component of 46Gy in 23 fractions. Once accrual triggers have been met, SBRT doses can be escalated in 1 Gy increments to a maximum of 22Gy in two fractions. Patient safety will also be measured with the rate of both acute and late moderate to severe Gastro-Intestinal (GI) and Genito-Urinary (GU) Common Terminology Criteria for Adverse Events (CTCAE) toxicities as well as patient reported quality of life. Efficacy will be assessed via biochemical control after 3 years.

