### Treatment delivery

Due to potential volume changes during a course of EBRT, as well as evidence of volume changes after HDRB, all patients should receive the boost component of their therapy prior to the fractionated EBRT component [19, 20].

The two SBRT boost fractions are to be separated by a 1 week break. The EBRT component is then to commence 2 weeks after the final boost fraction.

Preparation: Patient to continue same bladder preparation and enema regimen as used during simulation. Use Rectafix™ if utilised during simulation.

IGRT: On-line correction to gold fiducials, prostate and IDC with 0 mm action threshold. All effort should be made to commence treatment as soon as feasible after pre-treatment imaging has been performed.

During SBRT treatment: For techniques where real-time tracking or position monitoring is available (e.g. CK kV or intraprostatic transponders) this should be used. For other approaches, aim to perform repeat orthogonal imaging at least every 4 min, as there is evidence to support that 95% of patients will experience less than 3 mm of intrafraction motion over this timeframe [21]. Since most intrafraction motion will be either in the inferior-superior or anterior-posterior planes, only a lateral Electronic Portal Imaging (EPI) is necessary during treatment [22, 23].

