### Data collection

Patients will be assessed at baseline, the completion of treatment, 6 weeks post treatment, and then six monthly thereafter up to 5 years. At all visits, CTCAE GI and GU toxicity will be recorded. PSA will be measured at baseline, and then at all visits following treatment. The main efficacy endpoint is bNED calculated by the Phoenix definition of nadir+ 2 [24]. Any disease relapses or initiation of salvage treatments will also be recorded. Patient related quality of life (EPIC-26), and questionnaires regarding tolerance of treatment will also be collated at baseline, end of treatment, 12 months, 36 months and 60 months.

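### The dose-escalation rule applies its acute toxicity limit when 20 men have completed treatment, without requiring the 6-week CTCAE visit that is already scheduled

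*Protocol article*

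**What the plan says.** The escalation mechanism stands in the protocol article under SBRT treatment planning, after Fig. 3. Its toxicity condition reads "A minimum of 20 men in total are to complete treatment without > 15% suffering a grade 3 acute toxicity", and it also allows no grade 4 acute episode at that dose level. A second condition applies to each site: "The individual centre must also accrue ≥5 patients at the previous dose level prior to exploring dose escalation". The action follows directly: "Once this accrual trigger has been met, increase the dose by" 1 Gy. This can happen up to three times, to a maximum of 22 Gy. The abstract uses similar language in permissive form: "Once accrual triggers have been met, SBRT doses can be escalated in" 1 Gy increments.

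The visit schedule is under Data collection: "Patients will be assessed at baseline, the completion of treatment, 6 weeks post treatment, and then six monthly thereafter up to 5 years". On content it says "At all visits, CTCAE GI and GU toxicity will be recorded". CTCAE is therefore recorded at completion and again 6 weeks afterwards. The escalation rule refers only to completion and accrual.

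Two statements under Treatment delivery fix the timing: "The two SBRT boost fractions are to be separated by a 1 week break" and "The EBRT component is then to commence 2 weeks after the final boost fraction".

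**The concern.** The rule's milestones are completion for the 20 men and accrual for the centre's five. Neither requires that the men have reached the first visit after the whole SBRT and EBRT course. When the twentieth man finishes, he and others who finished in the preceding 6 weeks have been assessed only up to completion, yet they count in full in the denominator. The centre's five need not even have been treated.

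For a fixed group of men, a later assessment can add acute events but cannot remove any. The timing gap can therefore only make passing more likely. At stake is the safety of the next men, who would receive 1 Gy more before acute toxicity at the current level is fully known. The secondary objective under Objectives is that acute toxicity of grade 3 or higher should not rise with dose, so the rule bears directly on one of the trial's own aims.

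**Working it through.** The article states no error rate for the escalation rule, so there is no figure of its own to reproduce. The sample size of 268 rests on late toxicity and does not enter here.

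**Timing** (intervals from Treatment delivery and Data collection; five EBRT fractions a week is an assumption)
- Last boost fraction to completion: 2 + 23/5 = 6.6 weeks.
- Last boost fraction to the 6-week visit: 6.6 + 6 = 12.6 weeks.
- First boost fraction to the 6-week visit: 1 + 2 + 4.6 + 6 = 13.6 weeks.

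**What passes.** 15% of 20 is 3. So 3/20 = 15.0% passes and 4/20 = 20.0% fails.

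**Visits outstanding when the twentieth man finishes.** The article gives no accrual rate, so I assume a range. With k = finishers per month × 6/4.33:
- 2 a month: 2.8, taken as 3
- 4 a month: 5.5, taken as 6
- 8 a month: 11.1, taken as 11

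**Chance of passing.** Let p be the true acute grade 3 rate and f the share of those events first seen after completion; both are assumptions. The observed count is the sum of Binomial(20 − k, p) and Binomial(k, p(1 − f)). The rule passes if the sum is at most 3. The grade 4 condition is left out of this calculation.

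| p | f | k = 3 | k = 6 | k = 11 |
|---|---|---|---|---|
| 25% | 0 | 22.5% | 22.5% | 22.5% |
| 25% | 10% | 23.7% | 24.9% | 26.9% |
| 25% | 25% | 25.4% | 28.6% | 34.5% |
| 25% | 50% | 28.6% | 35.6% | 49.5% |
| 20% | 0 | 41.1% | 41.1% | 41.1% |
| 20% | 10% | 42.5% | 43.8% | 46.1% |
| 20% | 25% | 44.5% | 47.9% | 53.8% |
| 20% | 50% | 47.9% | 55.0% | 67.3% |
| 10% | 0 | 86.7% | 86.7% | 86.7% |
| 10% | 25% | 88.0% | 89.3% | 91.2% |

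The f = 0 rows are also the chances on complete data. In the middle case (k = 6, f = 25%) the gap adds 28.6 − 22.5 = 6.1 points at a true 25% and 47.9 − 41.1 = 6.8 points at a true 20%. An increase of 12 points or more does not need both extremes. At a true 25%, k = 11 with f = 25% adds 34.5 − 22.5 = 12.0 points, and k = 6 with f = 50% adds 35.6 − 22.5 = 13.1. At a true 10%, where passing is the right answer, the gap changes little.

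**The case against.** The strongest reply is that this is a journal article. The full protocol may define the acute window and the evaluable set, and the article never says that escalation may go ahead before acute toxicity has been assessed. Part of this stands. Whether men who stopped treatment early count towards the 15% is a detail that a condensed article may leave out, and I do not raise it. The timing point is different: the article sets out the operative mechanism, with its counts, limits and dose step, and ties it to completion and accrual.

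A second reply is that little remains unseen. Only the boost is escalated, and each of the 20 men is about 6.6 weeks past his last boost fraction with CTCAE recorded at completion. This also stands, and it limits the size. The credentialing run and real-time QA may take time, during which some 6-week visits will occur, so taking k at the moment the twentieth man finishes is a worst case. Those steps review plans, however, not observed toxicity.

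Third, much of the rule's weakness comes from its size: even on complete data, a true 20% rate passes 41.1% of the time. That is correct, and the change proposed here does not alter it.

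A reader might infer three stronger things that the text does not support:
- That escalation is triggered by accrual alone. The label suggests it, but the 15% grade 3 limit and the bar on grade 4 are part of the same rule.
- That escalation is compulsory once the trigger is met. The abstract's wording is permissive.
- That later events are lost. They are still recorded at the scheduled visits, so they are delayed.

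**Conclusion.** The point holds as a weakness in the timing of the safety check, and it should be fixed. As written, the limit on acute toxicity can be judged while the 6-week CTCAE visit is outstanding for recent finishers and for the centre's five men. The direction is certain: for the same men, the gap can only favour escalation. The size is not known and may be zero, because the article gives no accrual rate and no timing of acute events. Under the middle assumptions (6 visits outstanding, a quarter of grade 3 events late) the chance of passing an excessive rate rises by about 6 to 7 percentage points. It rises more with faster accrual or a larger late share, and hardly at all if few events are late. Confidence is medium, since the full protocol may already set a waiting period.

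**What to change.** Keep the thresholds and dose steps, and change when and on whom the rule is judged:
- Apply the 15% limit once at least 20 men at the dose level have had the 6-week post-treatment CTCAE assessment, with those assessed men as both numerator and denominator.
- Let any grade 4 acute event seen so far in any treated man at that level block escalation.
- Require the centre's five men to have completed treatment and had the 6-week assessment.

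The same men should form numerator and denominator. Counting grade 3 events at once but event-free men only after 6 weeks would bias the rate upward. For example, take 3 events in 20 assessed men plus 1 event in 11 recent finishers. That method gives 4/21 = 19.0%, whereas the rate to date among all 31 is 4/31 = 12.9%.

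The cost is a short wording change that uses a visit already in the schedule. The 20-man check comes up to about 6 weeks later per step, so at most about 3 × 6 = 18 weeks over the three steps. A centre waiting only on its own five men could wait up to about 13.6 weeks from the fifth man's first boost fraction.

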### Objectives

The primary objectives of the study are to determine the safety and efficacy of a SBRT prostate boost. Safety will be established if the cumulative rate of either acute or late GI or GU toxicity is equivalent to or less than previously reported in the HDRB or dose escalated IGRT EBRT literatures. Efficacy will be assessed via biochemical control after 3 years.

The secondary objective of the study is to ensure that the rates of grade 3 or higher acute CTCAE GI or GU toxicity does not increase with increasing dose delivery to the Clinical Target Volume (CTV).

Multicentre feasibility will be demonstrated if 3 or more centres contribute 5 or more patients to the study.

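### The acute-toxicity criterion only controls the next 1 Gy step, so as stated it has no effect at 22 Gy; secondarily, its entry conditions do not bar a level already in breach

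*Protocol article*

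**What the plan says.** The rule stands in the protocol article under SBRT treatment planning, in the text on stepwise escalation after Fig. 3. It has a trial-wide part, "A minimum of 20 men in total are to complete treatment without > 15% suffering a grade 3 acute toxicity", with a bar on any grade 4 acute event at that level. It also has a centre part: "The individual centre must also accrue ≥5 patients at the previous dose level prior to exploring dose escalation". When both are met, the dose rises by 1 Gy, and "This process can be followed a maximum of three times, to a maximum CTVsbrt-Urethral PRV D98 of 22 Gy". The Abstract (Methods) describes the same thing as a permission: "Once accrual triggers have been met, SBRT doses can be escalated in 1 Gy increments to a maximum of 22Gy in two fractions".

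Three other places bear on the point. The Objectives section sets a secondary objective to "ensure that the rates of grade 3 or higher acute CTCAE GI or GU toxicity does not increase with increasing dose delivery". Data collection schedules visits at baseline, completion of treatment, 6 weeks after treatment and then six-monthly, and says "At all visits, CTCAE GI and GU toxicity will be recorded". Table 2 limits organ doses. The rectal limits and bladder V19, V17 and V9 are fixed in Gy, while the bladder and urethral PRV maxima are percentages of the target dose. Its footnote adds: "Where Urethra has been limited to 19 Gy, these volumes may exclude the urethra".

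**The concern.** A numerical limit on acute toxicity is most needed at the highest dose, where there is least prior experience. Here the limit is attached only to the decision to go higher. At 22 Gy there is nowhere higher to go, so a grade 3 rate above 15%, or a grade 4 event, triggers nothing in the stated rule.

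A secondary form of the problem arises at 20 and 21 Gy. Centres will qualify at different times. A breach at 20 Gy blocks the move to 21 Gy, but a centre that later reaches its five patients at 19 Gy still meets each written condition for 20 Gy, because those conditions look at 19 Gy.

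At stake is whether more men could enter a level that fails the protocol's own limit. Comparing toxicity by dose after treatment can describe a rise, but it cannot prevent one, which is what the secondary objective aims to do.

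**Working it through.** **1. What each use of the rule judges** (escalation text, SBRT treatment planning).

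| Decision | Toxicity that is judged | Toxicity at the level being entered |
|---|---|---|
| 19 to 20 Gy | 19 Gy | not a condition |
| 20 to 21 Gy | 20 Gy | not a condition |
| 21 to 22 Gy | 21 Gy | not a condition |
| after 22 Gy | no decision remains | no stated consequence |

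Three steps use up the rule. The other safeguards in that text (dummy run, real-time QA of the first three plans at each level, external review before treatment) check plans. Table 2 constrains dose. None of them responds to toxicity that has been observed.

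**2. How many men could be affected.** The plan's own sample size reproduces: n = (1.96/0.05)² × 0.225 × 0.775 = 267.95, rounded up to 268. No allocation by dose level is given, so only ceilings follow, assuming the minimum of 20 men at each lower level:
- at 22 Gy: 268 − 3 × 20 = 208
- at 21 Gy, if a breach there blocks 22 Gy: 268 − 2 × 20 = 228
- at 20 Gy, if a breach there blocks 21 Gy: 268 − 20 = 248

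Centre minimums and parallel accrual at lower levels would reduce all three. They are not expected numbers.

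**3. How the criterion would behave if applied at every level.** The document gives no acute toxicity rate by dose, so the rates below are assumptions shown over a range. With 20 men, more than 15% means at least 4, since 3/20 = 15%.

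Grade 3 limb, one reading at 20 men, P(X ≥ 4) with X ~ Bin(20, p):

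| True grade 3 rate p | Pause | No pause |
|---|---|---|
| 10% | 0.133 | 0.867 |
| 15% | 0.352 | 0.648 |
| 20% | 0.589 | 0.411 |
| 25% | 0.775 | 0.225 |
| 30% | 0.893 | 0.107 |

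A single reading misses a true 20% rate 41% of the time, so one reading is not enough. As an illustration, add a second cumulative reading at 40 men, where more than 15% means at least 7. P(pause by then) = 1 − Σ P(X₁ = k) P(X₂ ≤ 6 − k), summed over k = 0 to 3, with X₁ and X₂ each Bin(20, p). This gives 0.17 at 10%, 0.49 at 15% and 0.77 at 20%. Misses at 20% fall to 0.23, and false pauses rise.

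Grade 4 limb, acting at any time, with grade 4 rate q and one grade 3 reading at 20 men. P(review by n men) = 1 − (1 − q)ⁿ × P(Bin(20, p/(1 − q)) ≤ 3). At q = 1% and p = 10%, the last factor is 0.863:
- n = 20: 1 − 0.818 × 0.863 = 0.29
- n = 40: 1 − 0.669 × 0.863 = 0.42
- n = 208: 1 − 0.124 × 0.863 = 0.89

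At p = 15% the first two are 0.48 and 0.57. At q = 0.5% the values at n = 20 are 0.22 (p = 10%) and 0.42 (p = 15%). With an open-ended grade 4 trigger, at least one review becomes likely at a large level even when grade 3 toxicity is acceptable.

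**The case against.** The strongest objection is that this is a condensed article and the text in question is an escalation rule. It says when to go up. Having no function where no step remains is what such a rule does, and suspension or closure provisions commonly sit in the full protocol. That limits the claim but does not remove it. The article gives the threshold, denominator, centre condition, step size and cap, and the point concerns how that stated rule operates. A reader might infer that the trial has no stopping rule; the article cannot support that, because the full protocol is not shown.

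The second objection is that the 20 men are counted across the trial and the wording is permissive, so a sensible sponsor would not open a breached level to another centre. This has force. The text neither instructs nor invites entry to a breached level; it merely does not prevent it. That is why this limb is secondary to the one at 22 Gy.

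Third, organ protection at the higher doses is real: rectal limits stay fixed in Gy, and the escalated volume excludes the urethral PRV. This may well reduce the rise in toxicity, but it does not react if a rise occurs.

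Finally, a reader might infer from the ceiling that about 208 men would be treated at 22 Gy without a limit. The document gives no accrual by level and does not support that. The probabilities above likewise describe the proposed rule at assumed rates, not the harm under the present one.

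**Conclusion.** The point holds in limited form. As stated, the acute-toxicity criterion governs only permission for the next step, so it judges 19, 20 and 21 Gy and has no stated effect at 22 Gy. On a literal reading it also leaves a breached 20 or 21 Gy level open to a later centre that qualifies below. This rests on wording, not on a calculation. The number of men who would be exposed is unknown, with 208 at 22 Gy as a ceiling only. Because the full protocol may already deal with it, this is a cheap improvement to a stated safety rule and not evidence that patients are unprotected. Nothing here changes the sample size of 268.

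**What to change.** Add to the escalation text that the same criterion applies at every open dose level, including 22 Gy:
- Grade 3 acute toxicity is read when the first 20 men at that level have reached the 6-week visit, and again at later reviews fixed in advance.
- Each grade 4 acute event prompts a review when it occurs.
- A breach pauses new entry to that level at all centres until the sponsor has reviewed it. New patients can meanwhile be treated at the last cleared level. At 19 Gy there is no such level, so the text should say what happens to new patients there.
- It should also say how men already planned or between fractions are handled.

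If the full protocol already has such a provision, a pointer to it is enough.

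The cost is a few sentences and some extra readings of toxicity that is already recorded at every visit; no extra patients are needed. Accrual at a level may be delayed, and men who enter before the 6-week reading are treated before its result is known. Some acceptable levels will be paused, at the rates worked out above, and each repeat reading adds to this. The action should therefore be a pause for review and not automatic closure.
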